### Blinding

The randomization will be blinded to the study team in order not to influence clinicians during the training webinar and other communications during the enrollment process. Participating clinicians will be unaware of the individual allocation of their patient until they have indicated the patient number on REDCap after consent is given and eligibility is confirmed. Due to the nature of chiropractic care, study participants (including clinicians and patients) cannot be blinded to the treatment.

### Sample size

There will be one primary comparison between the two study arms (SMC vs SCC) and a secondary comparison between those classified as DYS across study arms, anticipating that approximately half of each study arm will be classified as DYS. Based on the previous study [17], to detect a difference in the number of days with pain over 12 months [17] between the two main study arms corresponding to a medium Cohen’s effect size of 0.5, with an α-level of 0.05, power of 0.80, a sample consisting of 90 patients per arm would be required. Given that our study includes 2 arms and to account for potential dropouts (20%), our goal will be to recruit 220 patients [52]. Therefore, 15 clinicians will be recruited to collect data from 15 patients each.

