**Methods:**

This pragmatic randomized clinical trial will recruit 225 consecutive patients (18–65 years old) with significant (> 30 days in the past 12 months) recurrent spinal pain presenting to chiropractic clinics. After the initial 3 weeks (6 visits) of chiropractic care, patients will be randomized to receive either Stratified MC or Standard Chiropractic Care. Stratified MC: patients will complete the MAINTAIN instrument and be stratified to MC or symptom-guided care (clinicians’ judgment). Patients in the Standard Chiropractic Care arm will receive standard treatment based on the chiropractor’s judgment. The primary outcome is the total number of days with activity-limiting pain measured at 12 months. Secondary outcomes include the number of missed working days and loss of work productivity due to pain, pain intensity, disability, health-related quality of life, perceived improvement, and implementation of MAINTAIN instrument outcomes. An intention-to-treat protocol and generalized estimating equations (GEE) linear regression models will be used for analysis.

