Psychological [28, 29], behavioral [30], and social characteristics [31] of people with spinal pain are known to be important in the transition from acute to recurrent and persistent pain states [32–34]. The bio-psycho-social model is a framework that recognizes the influence of multiple interacting factors from different domains on spinal pain. Although not without limitations, it is the current leading framework guiding the management of spinal pain [31, 35–37]. Based on the cognitive-behavioral conceptualization of pain, the West Haven-Yale Multidimensional Pain Inventory (MPI) was developed to capture and measure the chronic pain experience [38]. The MPI instrument identifies three sub-groups [34] with similar characteristics within each sub-group. This classification has been shown to be reliable, valid, and useful in outcome-based research [39, 40]. The three different sub-groups are adaptive copers (AC; characterized by low pain severity, low interference with everyday life, low life distress, a high activity level and a high perception of life control), interpersonally distressed (ID; who tend to perceive negative responses by significant others to their pain behavior and complaints), and dysfunctional (DYS; characterized by high pain severity, marked interference with everyday life, high affective distress, low perception of life control and low activity levels) [38]. These sub-groups have been used in clinical settings to investigate neck and low back pain [41–43], temporomandibular disorders [44], headaches [45], fibromyalgia [46], and cancer pain [47] and have been associated with different clinical outcomes.

Secondary analyses of the data from the pragmatic RCT [48] revealed that patients in the DYS sub-group reported better outcomes from the MC approach. Specifically, these patients reported 30 fewer days with pain and an equal number of treatments compared to patients in the DYS sub-group who received the control (non-MC) intervention. Comparatively, patients in the ID and AC subgroup allocated to the MC treatment arm reported equal or more days with pain and 1.5 and 3.9 more treatments (respectively) compared to patients in the same MPI sub-group receiving the control intervention.

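### The printed sample-size inputs (d = 0.5, alpha 0.05, power 0.80) give 64 patients per arm, not the stated 90, and the recruitment target appears as both 220 and 225

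*Protocol article*

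**What the plan says.** The Sample size section names one primary comparison, between the stratified and the standard care arms. The difference in pain days over 12 months is expressed only in standardised form, "between the two main study arms corresponding to a medium Cohen’s effect size of 0.5", "with an α-level of 0.05, power of 0.80". No difference in days, SD or sidedness is given. From these inputs it concludes: "power of 0.80, a sample consisting of 90 patients per arm would be required".

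The section then inflates for loss: "to account for potential dropouts (20%), our goal will be to recruit 220 patients". The next sentence derives from this 15 clinicians contributing 15 patients each. The Abstract, under Methods, gives a different total: "This pragmatic randomized clinical trial will recruit 225 consecutive patients".

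The Randomization section allocates individual patients in equal numbers to the two arms, in blocks stratified by clinician. The Sample size section mentions no design effect, no division of alpha and no other adjustment.

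**The concern.** Effect size, alpha, power and sample size are tied together: any three fix the fourth. The protocol prints all four, and they do not agree. At least one is wrong, or an input that was used has been left out.

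What is at stake is interpretation. The stated power and detectable effect are what a reader uses to judge a null or imprecise result. As printed, a reader cannot tell whether the trial was sized for a medium effect at 80% power, for a medium effect at a higher power, for a smaller effect, or with an allowance that is not described. The two recruitment totals add a lesser doubt about which number counts as full enrolment.

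**Working it through.** **Inputs.** d = 0.5, alpha = 0.05, power = 0.80, one primary comparison, 20% dropout and a goal of 220 (Sample size); 1:1 allocation of individual patients (Randomization); 15 × 15 = 225 (Sample size) and 225 (Abstract). Sidedness is not stated, so both were tried.

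**Step 1: try to reproduce 90 per arm.** For two means, n per arm = 2(z₁₋α/₂ + z₁₋β)² / d².

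- Two-sided: 2 × (1.960 + 0.842)² / 0.25 = 62.8, so 63. The exact t-test gives 63.8, so 64.
- The plan's 90 is therefore not reproduced. It exceeds 64 by 26 patients per arm (26/64 = 41%).

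**Step 2: look for a variant that gives 90.**

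| Variant | n per arm |
|---|---|
| One-sided 0.05, power 0.80 | 50 (normal), 51 (t-test) |
| Two-sided, Mann-Whitney efficiency 0.955 | 67 |
| Two-sided, Mann-Whitney lower bound 0.864 | 74 |
| Alpha 0.025, power 0.80 | 78 |
| 64 already inflated for 20% dropout (64/0.8) | 80 |
| Alpha 0.05, power 0.90 | 86 |
| Alpha 0.0125, power 0.80 | 90 (normal), 91 (t-test) |
| Design effect 90/64 = 1.41 | 90 |

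Only the last two rows reach 90, and the protocol states neither input. With 15 patients per clinician, a design effect of 1.41 corresponds to an intraclass correlation of (1.406 − 1)/14 = 0.029.

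**Step 3: what 90 per arm gives if nothing else was used.**

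- Power at d = 0.5: Φ(0.5 × √(90/2) − 1.960) = Φ(3.354 − 1.960) = 0.918. The exact t-test gives 0.916.
- Effect detectable at 80% power: 2.80/√45 = 0.418. The exact t-test gives 0.420.

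**Step 4: dropout.**

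- 2 × 90 = 180 evaluable; 180/0.8 = 225.
- 225 × 0.8 = 180, exactly 90 per arm.
- 220 × 0.8 = 176, or 88 per arm, where power at d = 0.5 is 0.91.
- Multiplying instead of dividing, 180 × 1.2 = 216, does not give 220 either.

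**The case against.** **An unstated basis may exist.** The section cites a previous study and a further source, neither of which can be seen here, and the article condenses a fuller protocol. If a design effect of about 1.4 lies behind the 90, power at 90 per arm is 0.80, as printed. This stands in part. It means that 92% is not established as the trial's true power; it is only what the printed inputs imply. It does not rescue the statement as written, because the inputs are offered as sufficient for 90 and they are not. Because patients are randomized within clinician, a cluster inflation would also need a reason.

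**The mismatch is harmless.** On the printed inputs the trial is larger than it needs to be. That is correct, and it limits the seriousness.

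**220 is a rounding.** The shortfall is two patients per arm with almost no effect on power, and the operative figure of 225 is right. This also stands, so only the inconsistency remains.

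**Stronger readings to avoid.** A reader might infer that the subgroup comparison is underpowered. The section introduces it by "anticipating that approximately half of each study arm will be classified as DYS", which means about 45 per arm, and at d = 0.5 that gives a power of 0.65. But the protocol calls this comparison secondary, claims no power for it, and assigns d = 0.5 only to the main arms. A reader might also infer that a whole-arm d of 0.5 is implausible, since Background and rationale reports the benefit in the dysfunctional subgroup alone: "Specifically, these patients reported 30 fewer days with pain and an equal number of treatments". Turning that into a diluted effect requires an SD, no effect outside the subgroup, response in every patient and no maintenance care among controls. The documents state none of these.

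**Conclusion.** The sample-size statement is wrong as written. Its inputs give 64 per arm, not 90, and no variant confined to those inputs reaches 90. This assumes a two-sided comparison of two means with individual 1:1 allocation; a one-sided test widens the gap. The printed inputs do not underpower the primary comparison. The figures of 92% power at d = 0.5 and 80% power at d = 0.42 hold only if no further adjustment was made.

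The difference between 220 and 225 is real but minor. Taken together this is a reporting correction, not a design fault.

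**What to change.** State the actual basis for 90 per arm. If alpha was divided or a design effect applied, give its value and the reason, noting that randomization is within clinician. If there was no such input, restate the paragraph along these lines: *225 patients recruited, 180 evaluable (90 per arm) after 20% dropout, giving 92% power for d = 0.5, or 80% power for d = 0.42, two-sided alpha 0.05.* Replace 220 by 225 so that the Sample size section agrees with its own 15 × 15 and with the Abstract.

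The cost is wording only: no more patients and no change of procedure or analysis. The project timeline has recruitment running to May 2026 and analysis in the fall of 2027, so the correction can be on record before results are known.

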### Data collection

The automated SMS track, via Twilio System, will be used to collect SMS, and REDCap will be used to collect electronic questionnaire data. Each participating clinician will complete an initial questionnaire (Questionnaire 0-clinician) to record their individual characteristics.

Upon Questionnaire 0-patient completion, participating patients will be automatically registered in the Twilio system, given a confidential study ID linked to the clinician from which they are receiving treatment, and automatically scheduled to receive 3 questions via SMS every 2 weeks for 12 months. The follow-up questionnaires (Questionnaire 1–4) will be automatically sent via e-mail to both participating patients and clinicians at 3 weeks, 3, 6, and 12 months, respectively.

Data collection will be monitored daily in real-time, and contact with participating patients and clinicians will ensure high response rates. Specifically, in case of email delivery notification from REDCap or identification of incomplete questionnaires, email reminders will be sent to participating patients and clinicians.

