**Fig. 1 Fig1:**
[figure not shown]
Study flow and intervention arms

At their first visit prior to their appointment, participating patients will complete the first electronic questionnaire in REDCap (Questionnaire 0-patient), which includes the MAINTAIN instrument. Once patients complete Questionnaire 0-patient, their chiropractor will examine patients to determine final eligibility and complete Questionnaire 0-clinician also in REDCap.

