### Randomization

Participants will be randomly allocated to one of the two intervention arms at the first visit, as part of Questionnaire 0-clinician (immediately after eligibility criteria confirmation): Stratified Maintenance Care (SMC) or Standard Chiropractic Care (SCC), with the number of individuals equally balanced between groups. Central randomization will be performed, using block randomization stratified by clinician, performed by the study biostatistician ([name]) using SAS software. To ensure the allocation sequence is concealed from the researchers and participating clinics, varying block sizes of 2, 4, and 6 will be used. The unique randomization orders will be uploaded into REDCap (Research Electronic Data Capture system, Vanderbilt University, Tennessee) [51]. Each chiropractor will indicate, in their Questionnaire 0-clinician, the number of the patient (i.e., first patient enrolled = #1; second patient enrolled = #2, etc.), which will reveal that patient's group allocation. Importantly, chiropractors will only have access to the MAINTAIN instrument score for patients allocated to the MC group.

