### Outcome measures

Our primary outcome measure is the number of days with activity-limiting pain (recorded via SMS) measured bi-weekly over 12 months. Secondary outcome measures include missed working days due to pain, loss of work productivity due to pain, pain intensity, global perceived change, self-reported activity limitation, self-rated health, and pain self-efficacy. Table 2 shows all outcome measures recorded in the SMS and electronic questionnaires.

**Table 2 Tab2:** Summary of outcome measures

Time point	Questionnaire	Patient outcome measures	Clinician outcome measure
Every 2 weeks	SMS	- Total number of days with activity limiting pain in the past 2 weeks - Total number of missed workdays due to pain in the past 2 weeks - Experienced loss of productivity at work due to pain in the past 2 weeks	
First visit (baseline)	0	- Demographic data - Inclusion criteria - Pain intensity (NRS) [54] - Disability (Neck Disability Index [55]/Roland-Morris Disability Questionnaire [56]) - MAINTAIN instrument [49] - Health-related QOL (EQ-5D-5L) [58] - Self-efficacy (Pain Self-Efficacy) [59] - Physical Activity (IPAQ) [60] - Expectations	- Clinical impression - Implementation data
3 weeks	1	- Global Perceived Change [61] - Adverse events - Pain intensity (NRS) - Disability (Neck Disability Index or Roland-Morris Disability Questionnaire) -MAINTAIN instrument - Health-related QOL (EQ-5D-5L) - Self-efficacy (Pain Self-Efficacy) - Physical Activity (IPAQ) - Expectations	- Implementation data - Clinical impression - Date of visits and content (since last follow-up)
3 months	2		
6 months	3		
12 months	4		

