### Baseline and follow-up assessments

A summary of baseline and follow-up assessments is detailed in Table 2. Baseline data (Questionnaire 0) will be collected from both clinicians and patients at the first visit. Clinician data will include implementation data as well as their clinical impression of the patient. Patient data will be collected on demographics, current pain (numeric pain scale (NRS) [54]), pain in the past week (NRS), activity limitation/disability (neck disability index (NDI) [55]/Roland-Morris Disability Questionnaire (RMDQ) [56]), psychological and behavioral consequences of pain (MPI [57]), self-rated health (EQ-5D [58]), the MAINTAIN instrument [49], beliefs of patients on their ability to function with pain (pain self-efficacy questionnaire [59]), physical activity (International Physical Activity Questionnaire (IPAQ) [60]), and expectations of treatment.

Follow-up assessment (Questionnaire 1–4) will be completed at 3 weeks, 3 months, 6 months, and 12 months, also collecting data from clinicians and patients. Practitioners will provide data on implementation and clinical impression of the patient, as well as expectations of care if the patient is receiving MC (Yes/No), and the date and content of treatment visits. In addition to these questionnaires, patients will also receive an SMS every 2 weeks to collect data on activities limited due to pain in the last 0–14 days, missed working days due to pain, and loss of work productivity due to pain. Figure 2 presents the schedule of participating practitioners’ and patients’ enrollment, interventions, and assessments.

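### No baseline count of activity-limiting days is listed and the primary GEE has no baseline outcome term, so the primary comparison gives up precision that one questionnaire item could recover

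*Protocol article*

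**What the plan says.** The Outcome measures section defines the primary outcome as "the number of days with activity-limiting pain (recorded via SMS) measured bi-weekly over 12 months". In Table 2 the item "Total number of days with activity limiting pain in the past 2 weeks" stands in the SMS row only. The Questionnaire 0 row lists pain intensity, disability, MAINTAIN, EQ-5D-5L, self-efficacy, physical activity and expectations. The Baseline and follow-up assessments section lists the baseline content again, adding the MPI and past-week pain intensity, and again has no count of days.

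On timing, the Data collection section says "Upon Questionnaire 0-patient completion, participating patients will be automatically registered in the Twilio system", and from then on they are "automatically scheduled to receive 3 questions via SMS every 2 weeks for 12 months". The date of the first message is not given. Study procedure sets the order at the first visit: "Once patients complete Questionnaire 0-patient, their chiropractor will examine patients to determine final eligibility and complete Questionnaire 0-clinician also in REDCap". The Randomization section places allocation inside that clinician form: "Participants will be randomly allocated to one of the two intervention arms at the first visit". The Abstract says that patients are randomised after the initial three weeks and six visits. Under Interventions, allocated care begins only after those three weeks.

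The Data analysis plan models the primary outcome by linear GEE with terms for arm, time and arm by time, and adds a term for MC candidate (yes or no). No baseline value of the outcome is named.

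**The concern.** Patients enter with recurrent spinal pain, and it is reasonable to expect that recent days with limitation predict later days. A baseline count would therefore probably be a useful covariate. If it is not collected before allocation, two things are lost: the reduction in residual variance that adjustment would give, and the ability to show whether the arms started level on the outcome itself.

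This is a matter of data collection as well as modelling. A statistical analysis plan can choose covariates later, but it cannot recover an answer that was never requested.

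**Working it through.** **1. When is the first value obtained?** The item looks back two weeks, so the answer depends on two dates that the article leaves open or contradictory.

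| First message answered | Randomised at first visit (Randomization section) | Randomised after 3 weeks (Abstract) |
|---|---|---|
| At registration | Covers the two weeks before entry; a usable baseline if answered before the clinician form is completed | Usable pre-treatment baseline |
| At about week 2 | After randomisation, before allocated care starts | Before randomisation, but during initial care |

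The ordinary reading of a two-weekly schedule that starts at registration is a first answer at about week 2. Under first-visit randomisation that answer is not a clean covariate. Clinicians and patients are unblinded, chiropractors see the MAINTAIN score in the intervention arm only, and initial care follows clinicians' judgement. Allocation could therefore influence the answer. Questionnaire 0-patient comes before randomisation under either statement.

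**2. Does the stated sample size rely on baseline adjustment?** Inputs from the Sample size section: d = 0.5, alpha 0.05 (two-sided assumed), power 0.80, 90 per arm.

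- n per arm = 2(1.960 + 0.842)² / 0.5² ≈ 62.8, so 63 (64 by t-test). The stated 90 is not reproduced, which is a separate matter.
- With 90 per arm: 0.5 × √(90/2) = 3.354, and 3.354 − 1.960 = 1.394, giving power of about 92% before any clustering by clinician.

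So the main comparison does not depend on baseline adjustment.

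**3. What would adjustment be worth?** Let r be the correlation between the baseline count and the patient's 12-month mean, and p the share of patients who have the item. The documents give neither, so both are assumptions. Residual variance relative to no adjustment is 1 − p·r², and effective n = 180 / (1 − p·r²). At r = 0.5:

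- p = 1: 180 / 0.75 = 240
- p = 0.5: 180 / 0.875 ≈ 206
- p = 0.25: 180 / 0.9375 = 192

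Over a range of r:

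| r | all have item | half | a quarter |
|---|---|---|---|
| 0.3 | 198 | 188 | 184 |
| 0.4 | 214 | 196 | 188 |
| 0.5 | 240 | 206 | 192 |
| 0.6 | 281 | 220 | 198 |

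At r = 0.5 with full coverage, standard errors shrink by the factor √0.75 = 0.866, about 13%.

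**4. Discount for measures already collected.** The table compares adjustment with none. As an illustration only: if pain intensity and disability together already explain 16% of the variance and the count lifts this to 25%, effective n moves from 180/0.84 = 214 to 180/0.75 = 240. That is a gain of 12%, not 33%.

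**5. The secondary comparison.** The Sample size section expects about half of each arm to be DYS, so about 45 per arm. At d = 0.5: 0.5 × √(45/2) = 2.372, and 2.372 − 1.960 = 0.412, giving power of 66%. At r = 0.5 with full coverage: 2.372/0.866 − 1.960 = 0.779, giving 78%. Precision matters more here than in the main comparison.

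**The case against.** A reader might infer that no pre-randomisation value of the primary outcome exists or could ever be used. The documents do not establish that. Registration for text messages precedes the form that randomises, the first sending date is not stated, and the two statements on the time of randomisation disagree. Fig. 2, which may show the schedule, was not available for this review.

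A reader might also infer that the missing count is the strongest predictor of the outcome. The article gives no correlation, so that is unsupported.

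The lists may also be incomplete, since a journal article condenses the full questionnaire: the Baseline section names two items that Table 2 omits. Against this, the article introduces Table 2 as showing all outcome measures recorded by SMS and questionnaire, and both lists lack the count.

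Finally, pain intensity, disability and MAINTAIN are collected before randomisation, and the MC-candidate term carries part of that information. This stands, and it reduces the gain. But none of these is a count of activity-limiting days, and the entry criterion of more than 30 days in the past year concerns pain, not activity limitation.

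**Conclusion.** The point holds as a gap in baseline collection and adjustment. No baseline count of activity-limiting days is listed, no baseline outcome term is named, and on the ordinary reading the first value follows randomisation.

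A reader might go further and call the primary comparison biased or underpowered for this reason. Neither follows: randomisation protects the comparison, and 90 per arm gives about 92% power at d = 0.5 before clustering. The harm is wider intervals and a chance imbalance on the outcome that cannot be examined.

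At an assumed r of 0.5 and relative to no adjustment, the item is worth between about 12 extra patients (a quarter covered) and 60 (all covered) on a base of 180, and less beyond the measures already collected. Full coverage is no longer attainable if the item is added now, because the first patient was randomised in December 2023. The share already enrolled is not known from the article.

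**What to change.** 1. State when the first message is sent relative to randomisation, and reconcile the Abstract with the Randomization section.
2. If the first message is in fact answered before randomisation, say so and use that value as the covariate.
3. Otherwise add the two-week activity-limiting-days item to Questionnaire 0-patient for all further enrollees, and enter it in the primary GEE with a missing indicator for earlier patients. Missingness would follow enrolment date, and blocks of 2, 4 and 6 within clinician should keep it roughly balanced by arm.
4. For all patients, also adjust for baseline pain intensity and disability. If a patient completes only one of the two disability instruments, put the scores on a common scale or add an indicator for the instrument.

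The cost is one extra item in an existing electronic form, a protocol amendment, and covariates fixed before the data are analysed. The downside is that patients already enrolled lack the item, so the gain shrinks with the share enrolled before the change.
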